### Randomisation and blinding

Randomisation into three groups (cholecalciferol (D_3_), ergocalciferol (D_2_), or placebo) follows stratification of participants on the basis of age (two groups 30–50 and 51–75 years) and sex (male and female) into four groups, with a block size of 6 within each group.

In this double-blind trial, neither the participant, the investigators, nor the laboratory staff know whether participants have been allocated to vitamin D_2_, D_3_ or placebo during the course of the study. Since the IMPs are oil based or ethanol based products, in order not to compromise allocation concealment, the trial drug is administered by a person other than the investigator. The participants are also asked not to let the investigator know about any physical characteristics (including taste and feel) of the product that they have consumed.

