### Sample size

Sample size calculations showed that 207 participants (69 per randomised group) are required to detect a 0.2% difference in mean HbA_1c_ between the placebo and either vitamin D_2_ or vitamin D_3_ groups (power calculation was based on DCCT units) with 90% power and a 5% significance level, assuming a standard deviation of HbA_1c_ of 0.5%. However, given the importance of the secondary endpoint systolic blood pressure (SBP), a further calculation was performed to estimate the sample size that would be needed to detect a 5 mmHg difference in mean SBP between randomised groups, assuming a standard deviation of 16 mmHg. The assumptions for the sample size calculations were based on data from the ProActive trial [49] and the BanglaDip Study (personal communication). This yielded a requirement of 339 participants (113 in each group). Pragmatically, recruiting this larger number of participants will also mean that the study will still be powered for the primary endpoint (HbA_1c_) even if there are losses to follow up. Because 339 is not divisible by 6 (the block size for randomisation), the target number is 342 across the two test sites.

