### Statistical analysis plan

The analysis plan is available at http://www.mrc-epid.cam.ac.uk/files/2013/04/VitDtrial_AnalysisPlan_Sep2012.pdf. In brief, the primary analysis of efficacy endpoints uses an Intention-To-Treat (ITT) population, which includes all participants for whom outcome data are available, in the group to which they were randomised, regardless of the treatment actually received. A secondary analysis of efficacy endpoints uses a Per-Protocol (PP) population. This population excludes individuals who did not comply with the protocol (e.g. individuals who did not take all doses of the IMP). The analysis of safety endpoints uses a safety population, which includes all participants in the group based on treatment actually received. Any individual who received at least one dose of either vitamin D_2_ or vitamin D_3_ will be included in the vitamin D_2_ or vitamin D_3_ group.

Baseline characteristics of the study population will be summarised separately within each randomised group. For continuous variables, means and standard deviations will be presented, unless the variable has a highly skewed distribution, in which case, medians, 25^th^ and 75^th^ percentiles will be presented. For categorical variables, the number and percentage of participants within each category will be presented. For each variable (continuous or categorical), the percentage of missing values will be reported. No p-values will be calculated for these tables.

The primary efficacy endpoint, HbA_1c_, will be compared separately between each treatment group and placebo, using analysis of covariance with adjustment for baseline and centre. Where baseline values are missing, the missing indicator method [50] will be used to enable these participants to be included in the analysis. For both vitamin D_2_ vs. placebo and vitamin D_3_ vs. placebo, the difference in mean HbA_1c_, 95% confidence interval and p-value will be reported. An analysis will be performed to check whether adjusting for age and sex (the stratifiers) in the analysis of covariance model has any impact on the estimated treatment effects; if it has no impact, then they will not be included in the model. HbA_1c_ will be analysed and results will be reported in IFCC units (mmol/mol), and to enable those readers who are still using the DCCT% units, we will also provide equivalent results using the DCCT% units, derived using a previously described conversion formula [51].

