For each of the secondary efficacy endpoints, differences in means (for continuous endpoints) or proportions (for binary outcomes) between each treatment group and placebo, together with 95% confidence intervals, will be estimated using the same method described for the primary endpoint. Continuous endpoints with skewed distributions will be log transformed prior to analysis, in which case a ratio of geometric means (and confidence intervals) will be reported.

The number and percentage of participants experiencing any of the safety endpoints will be reported separately within each randomised group, without p values. For the primary endpoint, interactions between treatment group and baseline HbA_1c_, and treatment group and baseline vitamin D will be tested by including the appropriate interaction term in the analysis of covariance model. If the p-value for the interaction test is <0.05, the treatment effects and 95% confidence intervals will be estimated within subgroups defined by levels above and below the median value of either HbA_1c_ or vitamin D.

For the primary efficacy endpoint, two p-values will be calculated, one for the comparison of vitamin D_2_ vs placebo and one for the comparison of vitamin D_3_ vs placebo. No adjustment for multiple testing will be performed. An exploratory analysis will be performed in which mean HbA_1c_ will be compared between the vitamin D_2_ group and the vitamin D_3_ group, using the same method described above. An estimate of the difference in mean HbA_1c_ (adjusted for baseline), together with a 95% confidence interval, will be reported. For all other efficacy endpoints, the treatment effects (vitamin D_2_ vs placebo and vitamin D_3_ vs placebo) will be reported together with a 95% confidence interval. No p-values will be calculated. Interpretation of results for secondary endpoints will be cautious and results that are statistically significant in isolation will be interpreted less strongly than sets of results that are mutually supportive, or which are supported by previous research findings.

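### The rule that drops age and sex from the primary ANCOVA looks at the treatment estimate and not at its standard error; fixing the stratifiers in the model beforehand is a minor, almost free improvement

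*Protocol article*

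**What the plan says.** The section on randomisation and blinding describes "stratification of participants on the basis of age (two groups 30–50 and 51–75 years) and sex (male and female) into four groups". Allocation uses blocks of 6 in every stratum, and the three arms are allocated equally. Centre is not listed as a stratification factor.

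The statistical analysis section compares each vitamin D arm with placebo "using analysis of covariance with adjustment for baseline and centre". It then checks whether adding age and sex, which it identifies as the stratifiers, "in the analysis of covariance model has any impact on the estimated treatment effects", and states the consequence: "if it has no impact, then they will not be included in the model". The criterion is the estimate. The standard error is not mentioned.

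For the secondary efficacy endpoints, effects and intervals "will be estimated using the same method described for the primary endpoint", so the rule appears to carry over to systolic blood pressure (SBP) and the other continuous outcomes.

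**The concern.** Blocks of 6 within each stratum make treatment nearly orthogonal to age group and sex. Adding these covariates should therefore barely move the treatment estimate, however strongly they predict HbA1c. A check on the estimate then says little about whether they belong in the model. It tends to remove them for a reason unrelated to their value.

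Two things are at stake.

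- **Standard error.** Stratified randomisation already removes chance imbalance in age and sex from the sampling variability of the estimate. A model without the stratifiers leaves their variance in the residual, so it reports a standard error larger than the true one. Intervals are then too wide and the test is conservative.
- **Choice of model.** The primary model is settled after treatment effects have been estimated both ways. That is an avoidable weakness in an analysis that yields two primary p-values.

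**Working it through.** **Inputs from the protocol.** 342 participants, so 114 per arm; four strata; blocks of 6; HbA1c SD 0.5%; planned difference 0.2%; 5% significance, taken as two-sided; ANCOVA on baseline and centre.

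**Inputs assumed.** Loss of 10%. Two equal centres. Partial R², meaning the share of variance explained by age and sex beyond baseline and centre, of 0, 2, 5, 10 and 20%. The protocol gives no figure for partial R².

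**Step 1: residual SD.** The protocol's sample sizes are used only to calibrate the baseline correlation.

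- HbA1c: 2 × [0.5 × (1.960 + 1.282)/0.2]² = 131.3 per group, against 69 stated.
- SBP, same power and level: 2 × [16 × (1.960 + 1.282)/5]² = 215.2, against 113 stated.
- Both ratios are 0.525. That matches an ANCOVA factor 1 − r² with r = 0.69: 131.3 × 0.524 = 68.8 and 215.2 × 0.524 = 112.7, which round up to 69 and 113.

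The protocol does not state this correlation. It is adopted here because it reproduces both figures. The residual SD is then 0.5 × √(1 − 0.69²) = 0.362. With 0.9 × 114 = 102.6 per arm, the SE is 0.362 × √(2/102.6) = 0.0505. The simulation gave 0.0507.

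**Step 2: does the estimate move?** 10,000 simulated trials per row with no true effect; each comparison was fitted on its two arms. Shifts are in HbA1c percentage points.

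| Partial R² | Median shift | 95th percentile | Under ¼ SE | Under 1/10 SE |
|---|---|---|---|---|
| 0 | 0.0009 | 0.0037 | 100% | 98.3% |
| 2% | 0.0017 | 0.0065 | 99.8% | 89.2% |
| 5% | 0.0026 | 0.0088 | 99.0% | 76.5% |
| 10% | 0.0037 | 0.0117 | 95.5% | 61.6% |
| 20% | 0.0053 | 0.0161 | 83.9% | 43.3% |

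With no loss and R² of 5%, the shift was under a tenth of an SE in 98.4% of trials.

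**Step 3: does the standard error move?** In theory, omitting the stratifiers inflates the SE by 1/√(1 − R²), and the type I error becomes 2Φ(−1.96/√(1 − R²)). In the same simulated trials (without → with the stratifiers):

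| Partial R² | Mean model SE | True SD of estimate | Excess width, simulated (theory) | Type I, theory, without | Type I, simulated |
|---|---|---|---|---|---|
| 0 | 0.0507 → 0.0508 | 0.0508 → 0.0509 | −0.1% (0%) | 5.0% | 5.0 → 5.0% |
| 2% | 0.0507 → 0.0503 | 0.0504 → 0.0504 | 1.0% (1.0%) | 4.8% | 4.7 → 5.1% |
| 5% | 0.0507 → 0.0495 | 0.0492 → 0.0490 | 2.5% (2.6%) | 4.4% | 4.2 → 4.6% |
| 10% | 0.0508 → 0.0482 | 0.0485 → 0.0483 | 5.4% (5.4%) | 3.9% | 3.8 → 4.9% |
| 20% | 0.0508 → 0.0454 | 0.0462 → 0.0456 | 11.8% (11.8%) | 2.8% | 3.1 → 5.0% |

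The true SD is nearly the same either way. Only the model with the stratifiers reports it correctly. The Monte Carlo margin on a type I error near 5% is about 1.96 × √(0.05 × 0.95/10,000) = 0.4 percentage points.

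**Step 4: power, with 10% loss** (without → with).

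| Partial R² | True difference 0.2% (3,000 runs) | True difference 0.13% (5,000 runs) |
|---|---|---|
| 2% | 98.0 → 98.0% | 73.1 → 73.7% |
| 5% | 97.9 → 98.1% | 72.1 → 73.9% |
| 10% | 98.4 → 99.0% | 72.7 → 76.5% |
| 20% | 98.6 → 99.3% | 74.3 → 81.9% |

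The planned difference is 0.2%. The 0.13% column only shows what happens for a smaller effect.

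**The case against.** The strongest reply is that little is lost. The named default, ANCOVA on baseline and centre, is valid, and its error is on the safe side. The width excess exists only if age and sex predict 4-month HbA1c after baseline HbA1c and centre are in the model, and nothing in the protocol shows that they do. At the planned difference the trial has power to spare. All of this stands, and it sets the grade.

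Four stronger readings are tempting, and the protocol does not support them.

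- **The check is almost certain to find no impact.** That depends on a tolerance the article does not give. It holds for a quarter of an SE up to R² of 10%, but not for a tenth of an SE with losses. If impact meant a change of more than 10% in the estimate, then under no true effect and 10% loss the rule would add the stratifiers in about 31% of trials at R² of 2% and roughly two thirds at 20%. It behaves like never adding them only when the true effect is sizeable: 10% of 0.2% is 0.020, beyond the 95th percentile shift in every row of Step 2.
- **The intervals will be too wide.** They will be only if age and sex are prognostic.
- **The result could be biased or too often significant.** Omitting the stratifiers does neither. Choosing the model after seeing the effects is undesirable, but no inflation of false positives was shown.
- **The missing tolerance, or the adjustment for centre, is itself an error.** The article summarises a separate analysis plan that may define the tolerance. Adjusting for centre is legitimate, since recruitment and HbA1c laboratories differ by site.

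For the secondary endpoints no p-values are planned, so only interval width matters. Age and sex may predict SBP more strongly, but the protocol has no figure for it.

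What the objection does not rescue is the criterion: whatever the tolerance, it is applied to the estimate, while the gain lies in the standard error.

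**Conclusion.** The point holds as a minor one. The rule decides on a quantity that the design holds nearly constant and ignores the one that can change. It also leaves the primary model open until treatment effects are known.

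If age and sex have a partial R² of 2, 5, 10 or 20%, omitting them widens intervals by about 1, 2.5, 5 or 12% and brings type I error to about 4.7, 4.2, 3.8 or 3.1%. At the lower values, the practical effect on HbA1c is small. The estimate is unbiased.

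At a true difference of 0.2%, power changes by less than 1 percentage point, with larger losses only for smaller true effects. This rests on the inferred correlation of 0.69 and on 10% loss. A weaker correlation would leave less power in reserve and make the loss somewhat larger. The width and type I figures depend on partial R² and not on the correlation.

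**What to change.** Prespecify one primary model: HbA1c at 4 months on treatment group, baseline HbA1c, centre, age group and sex, with no data-dependent step. Use the same covariates, with each endpoint's own baseline, for SBP and the other continuous endpoints. Report the model without age and sex as a sensitivity analysis.

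The cost is one sentence in the protocol and the analysis plan, and two degrees of freedom. If age and sex explain nothing, keeping them costs nothing that matters: the ratio of standard errors without to with them was 0.999.

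### The test of treatment by baseline HbA1c is added to an ANCOVA with a missing indicator, so when both compared arms lack a baseline its result depends on an unstated fill-in constant

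*Protocol article*

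**What the plan says.** The Statistical analysis plan section compares HbA1c in each active arm with placebo "using analysis of covariance with adjustment for baseline and centre". It continues: "Where baseline values are missing, the missing indicator method [50] will be used to enable these participants to be included in the analysis". The efficacy population is one "which includes all participants for whom outcome data are available, in the group to which they were randomised", so a participant with an outcome but no baseline stays in.

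For the primary endpoint, the same section says that interactions of treatment with baseline HbA1c and with baseline vitamin D "will be tested by including the appropriate interaction term in the analysis of covariance model". The result has a stated use: "If the p-value for the interaction test is <0.05, the treatment effects and 95% confidence intervals will be estimated within subgroups", split at the median of the modifier.

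The article does not give the value put in place of a missing baseline. It does not mention a treatment by indicator term, and it does not limit the interaction tests to participants with a measured modifier. It refers to a separate full analysis plan, which was not available for this review.

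**The concern.** Each rule is acceptable alone; the difficulty is the combination. The missing indicator method replaces a missing baseline by a constant k and adds an indicator M. In a model without interaction, the coefficient of M takes up k, so the treatment effect is the same for any k.

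Once treatment × baseline enters, participants with M = 1 contribute to the product term as if their baseline really were k. If there is no treatment × M term, their treatment effect is forced onto the fitted line at k. When k lies far from the data, a few people with no measured baseline become high-leverage points for a slope about which they hold no information.

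At stake is the interaction estimate for baseline HbA1c and the p<0.05 rule that opens the subgroup estimates. A choice that makes no difference to the primary result could decide whether subgroup effects are shown.

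**Working it through.** **Plan's own figure.** The article gives none for the interaction test, so there is nothing to reproduce directly. Its HbA1c SD is used below.

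**Inputs from the article.** SD of HbA1c 0.5% (Sample size), about 5.46 mmol/mol. Target 342 in three groups, so 342/3 = 114 per arm. Analysis in IFCC units. Baseline mean 41 mmol/mol, borrowed from the high-risk trial described in the Background.

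**Assumed.** Slope of outcome on baseline 0.7, hence residual SD 5.46 × √(1 − 0.7²) = 3.9. Baselines missing completely at random, m per arm. Zero fill (k = 0). True interaction slope 0 or -0.40. Two-sided 5% test. The 0.7 is not out of line with the article: its inputs give 2 × (1.96 + 1.2816)² × (0.5/0.2)² = 131.3 per group, and the stated 69 follows if a baseline correlation of about 0.69 is allowed for (131.3 × (1 − 0.69²) = 68.8).

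**Algebra.** Model: y = a + bT + cx + eTx + dM, with x = k where M = 1. Let n = 114 − m be the number measured per arm. Least squares then averages two estimates of e:

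- the difference in slopes among measured participants, with weight w1 = (n − 1) × SD²/2 (in units of 1/residual variance);
- the difference between the treatment effects in measured and unmeasured participants, divided by (mean − k), with weight w2 = (mean − k)²/(2/n + 2/m). Its expectation is 0 when missingness is random.

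So the expected estimate is e × w1/(w1 + w2).

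- m = 1: w1 = 112 × 29.81/2 = 1669; w2 = 1681/(2/113 + 2) = 833; share 0.667; estimate -0.27.
- m = 2: w1 = 111 × 29.81/2 = 1655; w2 = 1681/(2/112 + 1) = 1652; share 0.500; estimate -0.20.

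**False positives.** For an unmeasured participant the baseline is not adjusted away. The residual variance is 3.9² + 0.7² × 5.46² = 15.21 + 14.61 = 29.82, which is 1.96 times what the model assumes. The true variance of the estimate exceeds the reported one by [w1 + w2² × (2/n + 2 × 1.96/m)/41²]/(w1 + w2).

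- m = 1: factor 1.317; 2 × P(Z > 1.96/√1.317) = 8.8%.
- m = 2: factor 1.471; 2 × P(Z > 1.96/√1.471) = 10.6%.

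**Power at a true -0.40.** Measured only: SE = 3.9/√1669 = 0.0955; Φ(0.40/0.0955 − 1.96) = 99%. Zero fill:

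- m = 1: SE = 3.9/√2503 = 0.078; Φ[(0.267 − 1.96 × 0.078)/(0.078 × √1.317)] = 90%.
- m = 2: SE = 3.9/√3306 = 0.068; the same formula gives 79%.

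**Simulation, 114 against 114.**

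| Handling | Estimate, 1 / 2 missing per arm | Power | False positives |
|---|---|---|---|
| Zero fill | -0.27 / -0.20 | 89% / 80% | about 9% / 11% |
| Mean fill, measured only, or zero fill with treatment × M | -0.40 / -0.40 | 98% / 98% | about 5% |

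Zero fill and mean fill disagreed on p<0.05 in 10% (m = 1) and 12% (m = 2) of data sets with no interaction, and in 9% and 21% with a slope of -0.40.

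**When nothing happens.** With k at the mean, w2 = 0. With missing baselines in only one compared arm, M absorbs that arm's unmeasured participants entirely; two missing in one arm and none in the other gave -0.40 and about 5% false positives.

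**Smaller baseline SD.** One entry route restricts HbA1c to 37-47 mmol/mol. With an assumed SD of 2.9 the shares are 471/(471 + 833) = 0.361 and 467/(467 + 1652) = 0.220, so the estimates are -0.14 and -0.09. Simulated power is 27% and 20%, against 59-60%.

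**Baseline 25(OH)D.** For assumed mean/SD of 45/25, 45/15 and 60/20 nmol/L, zero fill with one or two missing per arm shrinks the slope by only about 3-15%. A code such as 999 used as the fill would flatten either interaction, but nothing in the article suggests one.

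**The case against.** The strongest reply is that the article does not fix the faulty model. It names the missing indicator method in the paragraph on the main comparison and then speaks only of an appropriate interaction term. Zero fill is nowhere stated, mean fill would be sound, and the full plan may settle the matter. That stands as a limit on the size of the problem. It does not remove the point. The interaction term is to go into the ANCOVA that the section has just defined, indicator included, so the dependence on the constant follows from two stated rules.

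The trigger is also narrow. Baseline blood is to be taken from everyone at the first visit, and HbA1c is assayed fresh. Both compared arms must have a missing baseline. If two are missing at random across three equal arms, a given active-placebo pair has one in each with probability 2 × (1/3)² = 2/9; with three missing, the pair has at least one in each with probability 1 − 2 × (2/3)³ + (1/3)³ = 12/27. This stands too, although the article itself provides for missing baselines.

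Three stronger readings are tempting, and the article does not support them:

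- A reader might infer that the planned test is badly wrong as written. That needs a fill far from the data and missing baselines in both arms, neither of which is stated.
- A reader might extend the point equally to vitamin D. Baseline 25(OH)D is not a covariate in the stated ANCOVA, so applying the indicator to it is inference, and zero fill distorts it only mildly.
- A reader might infer that participants without a baseline would be counted below the median. Effects "will be estimated within subgroups defined by levels above and below the median value" of the modifier, and a participant with no measurement has no level.

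**Conclusion.** The point holds for the baseline HbA1c interaction, conditionally. Without a treatment by indicator term, the estimate and its p<0.05 rule depend on the fill-in constant whenever both compared arms contain a missing baseline. The size ranges from nil (mean fill, or missingness in one arm only) to the losses shown above for zero fill at the article's SD, and larger ones if the baseline SD is smaller. Zero fill, the counts of one or two per arm, the slope of 0.7, the true interaction of -0.40 and random missingness are all assumptions. The primary treatment effects, intervals and p-values do not change. This is a free improvement to a secondary analysis, not an error in the main result.

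**What to change.** Keep the missing indicator method for the main treatment comparisons. State that each interaction test, and any subgroup estimates that follow, use only participants with a measured value of that modifier, and report how many were left out. Alternatively, add a treatment by missing-indicator term to the interaction model, which makes the constant drop out. If the full analysis plan already says either, align the article's summary with it.

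The cost is one sentence. The excluded participants carry no information on how the effect varies with the modifier, and they remain in the primary analysis.
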